### Recruitment, Randomization, Blinding, and Treatment Allocation

Participants will be reimbursed with $25 for travel expenses (e.g., public transit, taxi, or parking) they incur to attend data collection appointments. Participants will be assigned using randomization to one of the two groups. The random allocation sequence will be computer generated (Random Allocation Software version 1.0). Blocked randomization will ensure equal numbers allocated to each group. Group allocation will be performed centrally by the principal investigator, who will not be involved in recruiting, scoring assessments, or administering the interventions (i.e., concealed allocation). Outcome measures will be obtained by a research assistant who will be blinded to group allocation. Participants are also blinded to group allocation since they will train on the same mechatronic device.

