#### Power and Sample Size Calculation

Since it is well established that perturbation training is effective in improving balance and reducing falls (Sherrington et al., 2019), the primary purpose of this study is to determine the effect of block PBBT on major components of reactive balance control among older adults: fall threshold and multiple-step threshold. Our primary hypothesis is that improvements in reactive balance control following block PBBT will be not inferior to the improvements following random PBBT. We will use the non-inferiority approach. Non-inferiority trials examine whether a new experimental treatment (i.e., block PBBT) is not unacceptably less efficacious than another treatment (i.e., random PBBT) already in use. Our primary outcome measures are the multiple-step threshold and fall threshold that are rarely used as outcome measures although multiple-step threshold levels are shown previously to be independent predictors of a future fall (Hilliard et al., 2008; Eichelberger et al., 2016) and the fall threshold is a novel measure of balance recovery function that seems to be ecologically valid. Both the fall threshold and multiple-step threshold were used as primary outcome measures in our recent study (Handelzalts et al., 2019) where we found that 11 of 11 stroke patients (100%) who participated in the random PBBT intervention improved their fall threshold (from 4.5 ± 2.0 to 6.5 ± 1.3) compared with only four out of 13 stroke patients who participated in the nonperturbation training intervention and that the multiple-step threshold to forward and backward perturbations was improved (from 1.9 ± 1.4 to 3.8 ± 1.7 and from 2.6 ± 1.4 to 4.5 ± 2.1, respectively). The sample size for a non-inferiority trial with a fall threshold and multiple-step threshold was calculated using the formula below (Statistical Solutions Ltd., 2020; nQuery 8—Power Sample Size for Group Sequential Trials version 8.6.1.0).

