Sample sizes for each of the primary outcomes are outlined in Table 4. In regard to the fall threshold and the multiple-step threshold (backward), the sample size that was calculated for each group is similar, *n* = 19. A two-group one-sided 0.05 significance level *t*-test will have 80% power to reject the null hypothesis that the block PBBT and random PBBT are not noninferior [the difference in means of the fall threshold and multiple-step threshold (backward), μR − μB, is 2.00 and 1.90, respectively, or farther from zero in the same direction), in favor of the alternative hypothesis that the means of the two groups, i.e., block PBBT and random PBBT, are noninferior, assuming that the expected difference in means is 0.00 and the common standard deviation for the fall threshold is 2.40 and the common standard deviation is 2.00 for the multiple-step threshold (backward; based on an earlier study; Handelzalts et al., 2019). In regard to the multiple-step threshold (forward), the calculated sample size in each group is 8, and a two-group one-sided 0.05 significance level *t*-test will have 80% power to reject the null hypothesis that the block PBBT and random PBBT are not noninferior (the difference in means, μR − μB, is 1.90 or farther from zero in the same direction), in favor of the alternative hypothesis that the means of the two groups are noninferior, assuming that the expected difference in means is 0.00 and the common standard deviation is 1.40 (Table 2). To account for attrition rates reported to be about 25% involving training in older adults, (McMurdo et al., 2000) it was decided to include 25 participants in each group (19 × 1.25 = ~25) for a total of 50 participants.

**Table 4 T4:** Sample size estimation.

	Fall threshold	Multiple-step threshold (forward)	Multiple-step threshold (backward)
Test significance level α (one-sided)	0.05	0.05	0.05
Non-inferiority limit difference, Δ0	2.00	1.9	1.90
Expected difference, Δ1	0.00	0	0.00
Δ0 − Δ1	2.00	1.90	1.90
Common standard deviation, σ	2.40	1.4	2.0
Effect size, δ = |Δ0 − Δ1|/σ	0.833	1.357	0.826
Power, %	80	80	80
Sample size, per group, *n*	19	8	19

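### Table 4, backward multiple-step threshold: a margin of 1.90 and SD of 2.0 give effect size 0.95 and n = 15 per group; the printed 0.826 and 19 need SD 2.3

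*Protocol article*

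**What the plan says.** The section Power and Sample Size Calculation sizes each primary outcome separately on a common design: "A two-group one-sided 0.05 significance level *t*-test will have 80% power", with an expected difference of zero. Allocation is 1:1 ("Blocked randomization will ensure equal numbers allocated to each group", in the section on randomization). The margins for the fall threshold and the backward multiple-step threshold are given as a difference that "is 2.00 and 1.90, respectively, or farther from zero in the same direction"; for the forward threshold it "is 1.90 or farther from zero in the same direction".

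For the backward threshold the text says "the common standard deviation is 2.00 for the multiple-step threshold (backward") and gives 19 per group. Table 4, in the row "Common standard deviation, σ", also has 2.0. It defines effect size as the absolute value of Δ0 − Δ1 divided by σ, and prints 0.826 and 19 for this column.

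The SDs are attributed to an earlier study in stroke patients. The figures quoted from it for the random-training arm are 4.5 ± 2.0 before and 6.5 ± 1.3 after for the fall threshold, and "from 1.9 ± 1.4 to 3.8 ± 1.7 and from 2.6 ± 1.4 to 4.5 ± 2.1, respectively" for the forward and backward thresholds. The article does not say whether the SDs in Table 4 are baseline, post-training, change or pooled values.

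On attrition of about 25%: "it was decided to include 25 participants in each group (19 × 1.25 = ~25").

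**The concern.** The effect size in Table 4 is a simple quotient of two entries in the same column. For the backward threshold it does not equal that quotient, and the sample size below it follows the wrong quotient, not the printed inputs. The text repeats the SD of 2.00, so damage to the table when the PDF was read does not explain it.

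Table 4 is the justification for 50 participants, and the backward threshold is one of the outcomes on which non-inferiority will be judged. A reader cannot tell which SD was assumed or what power that outcome was meant to have. The Limitations section says that this trial's data will inform the size of a larger one, so unclear SD assumptions could carry forward.

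**Working it through.** **Inputs.** From the text and Table 4: one-sided α = 0.05, power 80%, 1:1 allocation, true difference 0. Margin/SD: fall 2.00/2.40, forward 1.90/1.40, backward 1.90/2.0.

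**Method.** Effect size δ = margin/SD. Exact power of the two-group t-test with n per group uses the noncentral t distribution with 2n − 2 degrees of freedom and noncentrality δ√(n/2). The required n is the smallest that reaches 80%.

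**Step 1: reproduce Table 4.**

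| Column | δ from printed inputs | δ printed | n computed | n printed | Power at printed n |
|---|---|---|---|---|---|
| Fall | 2.00/2.40 = 0.833 | 0.833 | 19 | 19 | 80.9% |
| Forward | 1.90/1.40 = 1.357 | 1.357 | 8 | 8 | 82.5% |
| Backward | 1.90/2.0 = 0.95 | 0.826 | 15 | 19 | 89.0% |

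Two columns reproduce exactly, which confirms the method. The backward column does not.

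**Step 2: what would give the printed backward figures?** 1.90/0.826 = 2.30. With SD 2.3, δ = 1.90/2.3 = 0.826, n = 19 and power is 80.3%. A single changed entry, the SD, therefore restores both the effect size and n.

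**Step 3: other explanations with SD 2.0.**
- Normal approximation: n = 14.
- 90% power: n = 20.
- One-sided 0.025: n = 19. But δ would still be 0.95, the table states 0.05, and at 0.025 the fall and forward columns would become 24 and 10 instead of 19 and 8.

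None of these explains the column.

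**Step 4: basis of the SDs.** Setting Table 4 beside the quoted before/after SDs:
- Forward 1.4 equals the before value (after: 1.7).
- Fall 2.40 equals neither 2.0 nor 1.3.
- Backward 2.0, or 2.3, equals neither 1.4 nor 2.1.

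Read as change-score SDs, they imply a pre-post correlation r = (a² + b² − s²)/(2ab), where a and b are the before and after SDs and s is the Table 4 value:
- Fall: (4.00 + 1.69 − 5.76)/5.20 = −0.01.
- Forward: (1.96 + 2.89 − 1.96)/4.76 = 0.61.
- Backward: (1.96 + 4.41 − 4.00)/5.88 = 0.40, or 0.18 with 2.3.

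No single rule is visible. The choice of basis matters. With the quoted post-training SDs (1.3, 1.7, 2.1), n would be 7, 11 and 16. With a zero-correlation change score for backward, √(1.4² + 2.1²) = 2.52, n would be 23. These are sensitivity figures, not corrections.

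**Step 5: attrition.** 19 × 1.25 = 23.75, so 24. Allowing for a 25% loss, 19/0.75 = 25.3, so 26. From 25 per arm, 25 × 0.75 = 18.75 remain. Fall-threshold power at one-sided 0.05 is 79.0% with 18 per arm and 80.9% with 19.

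**The case against.** The strongest reply is that nothing hangs on the error. The fall threshold alone requires 19 per group and reproduces. At 19 per group the backward outcome has 89% power if the SD is 2.0 and 80.3% if it is 2.3, so the claim of 80% is met with either candidate. That stands, and it limits the point to a correction of the record. It does not remove the contradiction.

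Several stronger readings are tempting, and the documents do not support them:

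- A reader might infer that Table 4 as a whole fails. It does not: two of the three columns are exact.
- A reader might infer that n = 15 is the right figure. That holds only if SD 2.0 was the true input; 2.3 restores the rest of the column.
- A reader might infer that the three SDs have been shown to rest on different bases, for instance because √(2.0² + 1.3²) = 2.39 lies close to 2.40. This is conjecture. The article quotes SDs for one arm of 11 patients only. The Table 4 values could be pooled with the comparison arm, or be change-score SDs with different correlations.
- A reader might infer that the forward SD should be 1.7 because Statistical Analysis compares post-intervention values. The hypothesis speaks of improvements, so a change-score SD may have been intended, and the article does not settle it.
- A reader might bring in the lower power that follows if the 95% CI in Statistical Analysis is two-sided. That is a separate question about the significance level, not about the arithmetic of Table 4.

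On attrition, the article marks 25 as approximate, and 25 lies between 24 and 26. The slip is real but small.

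**Conclusion.** The backward column of Table 4, and the matching sentence in the text, are wrong as written. The stated SD of 2.0 gives effect size 0.95 and 15 per group, not 0.826 and 19; alternatively the SD should read 2.3. This is certain from the table's own formula. Which entry is wrong cannot be decided from the article.

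Two smaller points go with it. The kind of SD is unstated for all three outcomes and not evident from the quoted data. The attrition product does not equal 25, and 25 per arm leaves 18.75 expected completers, just under 19.

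The planned total of 50 need not change. This rests on the fall-threshold inputs as printed, on a backward SD of either 2.0 or 2.3, and on the stated one-sided 0.05. A materially larger backward SD, such as the 2.52 shown above, would need 23 per group, which is one more reason to state the basis.

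**What to change.** 1. State which SD was used for the backward threshold, and correct Table 4 and the text to one of two consistent sets: SD 2.0, effect size 0.95, n = 15 (89% power at 19 per group); or SD 2.3, effect size 0.826, n = 19 (80.3% power).
2. For each of the three SDs, say whether it is a baseline, post-training, change or pooled value and how it was obtained from the earlier study. Say how that basis relates to the post-intervention comparison in Statistical Analysis.
3. Replace the attrition product by the expected completers: 25 × 0.75, about 18 to 19 per arm, with fall-threshold power of about 79% to 81% at one-sided 0.05.

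The cost is a correction to one table and a few sentences, with no extra participants.

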### Statistical Analysis

Cohort descriptors and baseline values for primary and secondary outcomes will be compared between groups using Mann–Whitney *U* tests (continuous variables) or Fisher’s exact test (categorical variables). Measures that differ between groups at baseline may be used as covariates in the analysis of primary and secondary outcomes. To test the primary hypothesis, we will calculate the 95% CI for the post-intervention difference between groups (block PBBT minus random PBBT) for the primary outcomes [fall threshold and multiple-step threshold (backward and forward)]. Our hypothesis of non-inferiority will be supported if the lower limits of the 95% CIs are greater than the negative value of the non-inferiority limits (Schumi and Wittes, 2011). We will use both intention-to-treat and per-protocol analyses to test the primary hypothesis, as is recommended (Schumi and Wittes, 2011); per-protocol analysis will include only those participants who completed at least 80% of the training sessions. We will also use paired *t*-tests for each group individually to determine if the groups improve over time in the primary and secondary outcomes. To address the secondary objectives, we use analysis of covariance (ANCOVA) to compare the posttraining voluntary step execution test and postural sway parameters as well as the Berg Balance Score, Late-Life Function and Disability Index, and FES-I scores between groups, with the baseline value for each measure as a covariate. The dependent variable will be rank-transformed prior to conducting the ANCOVA to allow for nonparametric analysis.

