From a fall-prevention standpoint, an important aim of a PBBT is that learned motor skills (i.e., reactive balance performance) create a fast learning process, which can be generalized to a wide variety of everyday situations (i.e., real-life situations), which may require rapid balance recovery maneuvers. In general, motor learning research suggests that conditions during training should be varied randomly to optimize motor learning [challenge point framework (CPF; Guadagnoli and Lee, 2004)]. This would mean delivering perturbations from various directions in a randomized fashion during PBBT and different phases of the gait cycle. To our knowledge, no study has investigated whether a constant or random practice is more effective for motor skill acquisition, retention, and transferring motor tasks when older adults are training to improve their ability to recover from an unexpected loss of balance during walking. Our proposed study will incorporate similar principles with the use of a mechatronic device that can perturb participants unexpectedly and in multidirectional ways during treadmill walking. It is not known whether random PBBT better improves balance reactions in terms of the period of PBBT than block PBBT. In this research, we will address a key question about the generalizability of balance intervention and the underlying locomotor plasticity in older adults using random vs. block PBBT. The primary aim of this study is to determine the effect of block PBBT on reactive balance control among older adults (i.e., multiple- and fall-step thresholds). Our primary hypothesis is that improvements in reactive balance control following block PBBT will be not inferior to the improvements following random PBBT. The secondary purpose of this study is to determine the effect of block PBBT and random PBBT on balance proactive balance control and fear of falls. We hypothesize that, proactive balance, i.e., anticipatory balance control [Berg Balance Scale (BBS)] and fear of fall (FES-I), will cause similar effects in block PBBT and random PBBT.

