## Methods and Analysis

### Study Design and Setting

This is a double-blind randomized controlled trial (Figure 1, flowchart) that follows the recommendations of SPIRIT 2013 (see Supplementary Appendix 1 for the SPIRIT study checklist). Older adults are randomly assigned to one of two groups: (1) random PBBT; and (2) block PBBT. Both groups are trained twice a week for 4 weeks. Compensatory (reactive) and anticipatory (proactive) balance control during standing and walking, functional balance, and fear of falling will be measured pre-training and post-training. Fall monitoring will be performed 6 months after the posttest (Table 1). The PBBT will be provided inside participants’ community centers or in their protected housing. The study was approved by the Helsinki ethics committee at Soroka Medical Center, Beer-Sheva, Israel [Soroka Medical Center approval #0396-16-SOR; Israeli Ministry of Health (MOH)_#2018-07-22_003536; www.ClinicalTrials.gov, NCT04455607].

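### The primary non-inferiority interval has no prespecified baseline term, and covariates may be added after looking at baseline differences

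*Protocol article*

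**What the plan says.** All of this is in the Statistical Analysis section of the protocol article unless stated otherwise.

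- **Primary comparison:** "we will calculate the 95% CI for the post-intervention difference between groups (block PBBT minus random PBBT) for the primary outcomes". The outcomes are the fall threshold and the multiple-step threshold, backward and forward. Non-inferiority is "supported if the lower limits of the 95% CIs are greater than the negative value of the non-inferiority limits".
- **Covariates:** the section opens with baseline testing of the randomised groups: "Cohort descriptors and baseline values for primary and secondary outcomes will be compared between groups using" Mann–Whitney or Fisher tests. Then: "Measures that differ between groups at baseline may be used as covariates in the analysis of primary and secondary outcomes".
- **Secondary outcomes:** these are compared by ANCOVA "with the baseline value for each measure as a covariate", on ranks.
- **Hypothesis (Background):** "improvements in reactive balance control following block PBBT will be not inferior to the improvements following random PBBT".
- **Availability of baseline:** under Study Design and Setting, reactive balance is among the measures that "will be measured pre-training and post-training". Table 1 places the balance assessment at T1 and T2.

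**The concern.** The one comparison that decides the trial is the one with no prespecified baseline term. The baseline threshold is collected on everyone, probably predicts the post-training threshold, and is the reference point for an improvement. In a trial planned on 19 completers per arm, leaving it out widens the interval. It also lets whichever group happened to start better carry part of that head start into the estimate.

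The covariate rule does not repair this. It responds only to imbalances that are noticed, and the word may leaves the choice open until the data are seen. At stake are the width of the interval set against the margin, and whether the primary model is fixed in advance.

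**Working it through.** **Inputs from the documents** (Power and Sample Size Calculation, Table 4): fall-threshold margin 2.00, expected difference 0.00, common SD 2.40, one-sided α 0.05, 19 per group. The earlier study in stroke patients gave a fall threshold of 4.5 ± 2.0 before and 6.5 ± 1.3 after random training.

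**Assumptions:** the pre-post correlation r is not given, so 0.3 to 0.7 is used. The 95% interval is read as two-sided. In steps 1 to 3, 2.40 is taken as the post-training SD.

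**1. The plan's own figure.** Standard error of the difference = 2.40 × √(2/19) = 0.779. Noncentrality = 2.00/0.779 = 2.57 on 36 degrees of freedom. At one-sided 0.05 the power is 80.9%, and the noncentral-t calculation returns 19 per group, as stated. The planned test is therefore an unadjusted two-group t-test.

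**2. The stated decision rule, unadjusted.** Half-width of the 95% interval = 2.028 × 0.779 = 1.58 levels. Power at 19 per arm (one-sided 0.025) = 70.5%.

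**3. With prespecified baseline ANCOVA.** Residual SD = 2.40 × √(1 − r²), with 35 degrees of freedom.

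| r | Variance removed (r²) | Residual SD | Half-width | Power |
|---|---|---|---|---|
| none | 0 | 2.40 | 1.58 | 70.5% |
| 0.3 | 9% | 2.29 | 1.51 | 74.5% |
| 0.5 | 25% | 2.08 | 1.37 | 82.2% |
| 0.7 | 49% | 1.71 | 1.13 | 93.8% |

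**4. Sensitivity to the SD.** If the post-training SD is 1.3, the standard error is 1.3 × √(2/19) = 0.42, the unadjusted half-width is 2.028 × 0.42 = 0.86, and power is 99.6%. The share of variance removed is still r², but almost no power is left to gain. The documents do not say which quantity 2.40 describes. It is close to √(2.0² + 1.3²) = 2.39, the SD of a change score at zero correlation, but that is only an inference.

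**5. How much imbalance carries over.** With a baseline SD of 2.0, the chance difference at baseline has SD 2.0 × √(2/19) = 0.65 levels, so a 95% range of 1.96 × 0.65 = ±1.27. It reaches the post-training difference multiplied by the slope, r × (post SD / baseline SD):

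- post SD 2.40: ±0.46, ±0.76, ±1.07 levels at r = 0.3, 0.5, 0.7;
- post SD 1.3: ±0.25, ±0.41, ±0.58.

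The margin is 2.00.

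**6. The covariate rule.** A simulation (40,000 trials per setting, 19 per arm, normal data, SD 2.40, adjustment only when Mann–Whitney p < 0.05) adjusted in about 5% of trials. Power was 70%, 71% and 72% at r = 0.3, 0.5, 0.7, so the rule recovers almost nothing.

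At r = 0.5, among trials with a non-significant baseline imbalance larger than one standard error:

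| True difference | Block starts worse | Block starts better | ANCOVA, either way |
|---|---|---|---|
| 0 (non-inferiority declared) | 43% | 91% | about 80% |
| −2.00 (falsely declared) | 0.2% | 7.7% | about 2.5% |

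Averaged over all randomisations, type I error was about 2.5% for the raw comparison and 1.8% to 2.4% for the test-triggered rule.

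**The case against.** The strongest reply is that nothing here is invalid. Randomisation makes the raw post-training difference unbiased. Because expected baselines are equal, it estimates the same quantity as a difference in improvements. Overall type I error is held, as step 6 shows. All of this stands, so a reader who infers that the verdict is biased or the error rate inflated goes further than the documents allow.

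Two other strong readings also fail. One is that a baseline imbalance passes in full into the result: it passes only by the pre-post slope, and the most extreme imbalances are those the covariate rule could catch. The other is that adjustment would restore all the power lost by using a 95% interval after planning at one-sided 0.05. The loss is 80.9 − 70.5 = 10.4 points. At r = 0.3 ANCOVA returns 74.5 − 70.5 = 4.0 of them, about 38%; full recovery needs r near 0.5 or more.

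It can also be said that the size of the gain is unknown, since the protocol gives neither r nor a clear meaning for 2.40. That is right, and with an SD of 1.3 the power argument nearly vanishes.

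Finally, the Abstract mentions a rank-transformed ANCOVA without limiting it to secondary outcomes. It names no covariate, and ranks would not yield an interval in levels to set against the margins, so it does not supply the missing term.

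The objection does not reach the wording itself. The article states the estimator, the decision rule and the covariate rule, so this is not detail left to a fuller document.

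**Conclusion.** The concern holds in a limited form. The primary interval rests on a raw post-training difference with no prespecified baseline term, and the route by which covariates may enter is driven by the data and optional. The consequences are lost precision (a fraction r² of the variance), a verdict that depends on chance baseline imbalance in the trial at hand, and discretion over the primary model. Bias and an inflated overall type I error are not among them.

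With 2.40 as the post-training SD, the power gain at 19 per arm is about 4, 12 and 23 points at r = 0.3, 0.5 and 0.7. It is close to nil if that SD is 1.3. The direction of the precision gain over this range does not depend on the SD; its practical size does. Confidence is high on the wording and modest on the size. The change is worth making because it is free, not because the present analysis is unsound.

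**What to change.** - Make the primary analysis an ANCOVA of each post-training threshold on group and the same threshold at T1, on the original level scale. Ranks would not do, because the limits of 2.00 and 1.90 are in levels.
- Take the 95% interval for block minus random from that model and compare it with the stated limits.
- Delete the rule that selects covariates from baseline comparisons. If any further covariate is wanted, name it before the data are seen.
- State whether the SD of 2.40 refers to post-training values or to changes. With the same baseline covariate, ANCOVA gives the same group effect for either outcome, so the primary analysis itself is unaffected.

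The cost is a change of wording and one degree of freedom per model. No new data and no change in sample size are needed.

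### Power is computed for a one-sided 0.05 test, but non-inferiority is judged on a 95% CI, so fall-threshold power at 19 per group is 70.5%, not 80%

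*Protocol article*

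**What the plan says.** The Power and Sample Size Calculation section of the protocol article bases the sample size on a "two-group one-sided 0.05 significance level" t-test that "will have 80% power to reject the null hypothesis" of inferiority. Table 4 repeats one-sided 0.05 in all three columns. The margins are 2.00 for the fall threshold and 1.90 for each multiple-step threshold, and the expected difference is 0. The calculation gives 19 per group for the fall threshold, 8 for the forward multiple-step threshold and 19 for the backward one. Enrolment is set at 25 per group to allow for about 25% attrition.

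The Statistical Analysis section then fixes a different test. It says "we will calculate the 95% CI for the post-intervention difference between groups (block PBBT minus random PBBT"), lists the fall threshold and the backward and forward multiple-step thresholds as primary outcomes, and regards the single hypothesis as supported if the "lower limits of the 95% CIs are greater than the negative value of the non-inferiority limits". The section does not describe the interval as one-sided. It also does not say whether one outcome or all three must succeed.

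**The concern.** The lower limit of a conventional 95% CI is a one-sided 0.025 bound; a one-sided 0.05 test matches a 90% CI. The 80% in Table 4 therefore describes a test that the analysis section does not use, and the test it does use is stricter.

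Two things are at stake. First, the chance of missing true non-inferiority is larger than the plan says, and such a failure could be misread as evidence against block training. Second, with two confidence levels in one protocol, the choice between 90% and 95% could be made after the data are seen. In a non-inferiority trial that choice is the evidential standard.

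A related gap is that 80% power was computed for each outcome alone, while the rule covers three outcomes under one hypothesis.

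**Working it through.** **Inputs** (Table 4 and the text above it): margins 2.00 (fall), 1.90 (forward) and 1.90 (backward); true difference 0; SD 2.40 (fall), 1.40 (forward) and 2.0 (backward); 19 evaluable and 25 enrolled per group; equal allocation.

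**Formula.** Two-sample t-test with n per group: df = 2n − 2, noncentrality = (margin/SD) × √(n/2), and power = P(noncentral t > t critical at 1 − α).

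**Reproducing the plan at one-sided 0.05.**
- Fall: 2.00/2.40 = 0.833. The smallest n reaching 80% is 19 (80.9%). Matches.
- Forward: 1.90/1.40 = 1.357. The smallest n is 8 (82.5%). Matches.
- Backward: the printed SD gives 1.90/2.0 = 0.95 and n = 15, which does not match. The printed effect size 0.826 implies SD 1.90/0.826 = 2.3 and gives n = 19 (80.3%), which does. Table 4 contradicts itself here, so both readings are carried below.

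**Applying the 95% CI rule (one-sided 0.025).**

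| Outcome | Power, n = 19, 0.05 | Power, n = 19, 0.025 | n per group for 80% at 0.025 | Power, n = 25, 0.025 |
|---|---|---|---|---|
| Fall | 80.9% | 70.5% | 24 | 82.3% |
| Forward | 99.3% | 98.3% | 10 | 99.7% |
| Backward, SD 2.0 | 89.0% | 81.3% | 19 | 90.8% |
| Backward, SD 2.3 | 80.3% | 69.8% | 25 | 81.6% |

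The fall threshold shows where the loss comes from. With n = 19 and SD 2.40, the standard error is 2.40 × √(2/19) = 0.779. The critical values on 36 df are 1.688 (90% CI) and 2.028 (95% CI). The lower limit clears −2.00 if the observed difference exceeds −2.00 + 1.688 × 0.779 = −0.69 under a 90% CI, but −2.00 + 2.028 × 0.779 = −0.42 under a 95% CI. The chance of missing true non-inferiority on this outcome rises from 19.1% to 29.5%.

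**Joint power, if all three must pass.** The document gives no correlation between outcomes, so 0 to 0.8 is assumed. At correlation 0, joint power is the product of the three powers. Higher correlations were simulated with three equally correlated normal outcomes.
- n = 19, 0.025, SD 2.3: 0.705 × 0.983 × 0.698 = 0.48, rising to 0.61 at correlation 0.8.
- n = 19, 0.025, SD 2.0: 0.705 × 0.983 × 0.813 = 0.56, rising to 0.67.
- n = 19, 0.05: 65–73% (SD 2.3) or 71–78% (SD 2.0).
- n = 25, 0.025: 67–75% (SD 2.3) or 75–80% (SD 2.0).

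**The case against.** **The rule errs on the safe side.** The 95% CI is stricter than the alpha used for sizing, so the mismatch does not make a false claim of non-inferiority more likely. This stands. The error is in the stated power, not in the protection against a wrong positive.

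**With no dropout the problem nearly disappears.** If all 25 per group are analysed, each outcome alone exceeds 80% at one-sided 0.025. This is also true, but the plan adds participants because it expects about 25% attrition, so 19 is its own evaluable number.

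**The 95% CI might mean a one-sided 95% bound.** That would remove the alpha conflict, but the text does not say so. If all three outcomes must pass, joint power at 19 per group would still be below 80%.

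**The study is small by its own account.** The Limitations section says it has a pilot character and will inform a larger trial. That softens the consequence. The methods still present a powered non-inferiority test, and its power should match its rule.

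**Two stronger readings are tempting and should not be drawn.**
- A reader might infer that every primary outcome drops to about 70%. The document's figures do not support that: forward stays at 98.3%, and backward is 81.3% with the SD printed in both the text and Table 4.
- A reader might take it as written that all three outcomes must pass. The plural limits under one hypothesis read most naturally that way, but the word all does not appear, and the rule could be applied outcome by outcome. If any single outcome sufficed, the issue would instead be three unadjusted chances of success.

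**Conclusion.** The contradiction holds: the sizing uses one-sided 0.05 and the decision rule uses one-sided 0.025. The firm consequence is for the fall threshold, where power at 19 per group is 70.5% rather than 80%, and 24 evaluable per group would be needed. This uses only printed inputs and a true difference of 0.

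The backward outcome is short of 80% (69.8%) only if the effect size 0.826 is right; with SD 2.0 it reaches 81.3%. The forward outcome is unaffected in practice.

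Joint power at 19 per group, about 48–67% across both backward readings, is conditional on three things: an all-must-pass rule that is not written, assumed correlations of 0 to 0.8, and the unresolved backward SD. It is a range and should not be quoted as a single settled figure.

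**What to change.** Keep the 95% CI rule and the 50 participants, and change the following:

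1. In the Power and Sample Size Calculation section and Table 4, replace one-sided 0.05 by one-sided 0.025. Give power for each outcome separately at 19 evaluable per group: fall 70.5%, forward 98.3%, and backward once its entry is settled. The values at 25 per group can stand beside them. A single figure for all outcomes would be wrong.
2. Reconcile the backward SD (2.0) with the backward effect size (0.826), and recompute that column.
3. State in the Statistical Analysis section whether all three outcomes must pass. If so, report joint power as a range with the assumed correlations. If not, state how multiple chances of success are handled.

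If one-sided 0.05 was intended, change the decision rule to a 90% CI and justify that level. The fall-threshold figure of 80% then stands, but items 2 and 3 remain.

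The cost is wording and a less favourable stated power. No extra participants are needed.
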